# 4.0 Selection and Enrolment of Volunteers

Volunteers will be recruited from the database of healthy volunteers maintained by Q-Pharm, or by advertisement to students of The University of Queensland or to the general community, as approved by the Queensland Institute of Medical Research Human Research Ethics Committee (QIMR-HREC) and other respective IRBs reviewing the protocol.

## 4.1 Inclusion Criteria

1. Males or females between 18 and 45 years, inclusive.
2. Participants must be in good health, as assessed during pre-study medical examination and by review of screening laboratory tests.
3. Available for the duration of the trial (maximum of 52 weeks).
4. Participants must understand the procedures involved and agree to participate in the study by giving fully informed, written consent.
5. Agree to not donate blood during the course of the trial
6. Be contactable by telephone throughout the study

## 4.2 Exclusion Criteria

Participants may be excluded from the study either during screening, on vaccination days, or during the blood sampling intervals, for any of the following reasons:

1. History of malaria or malaria exposure within last two years
2. Travelled to or lived (>2 weeks) in a malaria-endemic country during the past 12 months or planned travel to a malaria-endemic country during the course of the study.
3. Significant intercurrent disease of any type, in particular liver, renal, cardiac, pulmonary, neurologic, rheumatologic, or autoimmune disease by history, physical examination, and/or laboratory studies including urinalysis.
4. Evidence of acute illness within the four weeks before trial prior to screening.
5. Use of corticosteroids, anti-inflammatory drugs, any immunomodulators or anticoagulants. Currently receiving or have previously received immunosuppressive therapy, including systemic steroids including ACTH or inhaled steroids in dosages which are associated with hypothalamic-pituitary-adrenal axis suppression such as 1mg/kg/day of prednisone or its equivalent or chronic use of inhaled high potency corticosteroids (budesonide 800 µg per day or fluticasone 750 µg).
6. Medical requirement for intravenous immunoglobulin or blood transfusions
7. History of a severe allergic reaction or anaphylaxis or convulsions following any vaccination.
8. Receipt of a live vaccine within past 4 weeks or a killed vaccine within past 2 weeks prior to entry into the study.
9. Participation in any clinical trial within the 4 weeks preceding the study.
10. Alcohol consumption greater than community norms (i.e. more than 21 standard drinks per week for males, or more than 14 standard drinks per week for females).
11. A history of drug habituation, or any prior intravenous usage of an illicit substance.
12. Smokers (>20 cigarettes/day) or those who are unable to refrain from smoking during the periods of confinement in each period of the study.
13. Positive test for HIV, hepatitis B, hepatitis C, or any clinically significant biochemical or haematological abnormality or any clinically significant abnormality in urinalysis.
14. Participant unwilling to regulate vigorous exercise within the vaccination period.
15. Female participant unwilling to use reliable contraception methods for the duration of the trial.
16. Pregnancy confirmed by a positive serum or urine human chorionic gonadotropin (ß-HCG), or breast-feeding or lactating females
17. Blood donation during the 8 weeks preceding the study.
18. Receipt on any investigational product four weeks prior to screening.
19. History of a known allergy to nickel.

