### 2.3.2 Clinical Experience with Other MSP2 Vaccines

The MSP2-C1 combination vaccine formulation that will be used in this study has not yet been tested in human trials. However, both Phase 1 and Phase 2 studies have been carried out previously with vaccines containing a recombinant form of 3D7 MSP2 known as Ag1624. Ag1624, like the forms of MSP2 in the current vaccine was expressed in *E. coli* and was purified by a series of chromatography steps. Ag1642 differs from EcMSP2-3D7 and ECMSP2-FC27 in that the hexa his tag is located at the N-terminus rather than the C-terminus. Also, a small number of additional residues encoded by the plasmid cloning vector are present at both the N- and C-terminus in Ag1624.

Recombinant MSP2 was injected into humans for the first time when Ag1624 in combination with recombinant CS protein (Combination A), formulated with alum was tested in healthy Swiss volunteers (20). Thirty three participants received two low (20 g) or two high (100 g) vaccinations intramuscularly, while six volunteers received placebo (alum alone). Twenty-six participants reported 51 immunisation-related adverse events, mainly pain at the injection site. There were no serious adverse events and the vaccine was considered safe for further evaluation. However, the development of this vaccine ceased because immune responses were poor and no protection was observed among five subjects who were experimentally challenged with *P. falciparum*.

Subsequently, a series of Phase 1 and 2 trials were carried out with a combination of three recombinant antigens (Combination B) that included 3D7 MSP2. In addition to Ag1624 Combination B contained 190L (a small fragment of MSP1) and Ag1505 (a large fragment of RESA). All three components of Combination B were formulated as a water-in-oil emulsion with Montanide® ISA720, the adjuvant to be used in this study. Two Phase I vaccine trials were conducted at the Royal Brisbane Hospital to test the immunogenicity and safety of the Combination B vaccine in healthy Australian volunteers (21).

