The most common adverse event observed in trials using Montanide ISA720 is local reactogenicity (34). The acute reactions are characterized by of pain, swelling, induration, sterile abscess, and granuloma formation. These have been generally mild to moderate in 33 to 91% of volunteers. In the single Phase 2 trial in children in an endemic area the rate was 12% (26). The overall rate for mild and moderate acute local reactions is similar to that observed with licensed pediatric vaccines such as DT (standard pediatric dose) (55% mild/moderate local reactions) or dT (low dose vaccine) (52% mild/moderate reactions) in 6-year-old children. Severe local reactions occurred only with 5 vaccinees who received the vaccine via the intramuscular route for a cumulative rate of 1%. This proportion is not greater than that observed for some licensed vaccines (17% severe local reactions with DT and 11% severe local reactions with dT) (35). Severe local reactions were seen much more commonly in trials administering the vaccine subcutaneously. In these 2 trials (30) up to 44% of recipients of higher doses were not revaccinated due to local reactions. Acute local reactions were seen frequently with pain, swelling and/or induration most common. In the HIV vaccine study (33) sterile abscess and granuloma formation was seen in some volunteers, particularly those receiving the high antigen dose (2 mg), which was far in excess of that given in the malaria vaccine studies or that planned in this study. In most studies the vaccine was injected intramuscularly and when this route was used the majority of local reactions were mild to moderate with a cumulative rate of 1% for severe reactions. In contrast, severe local reactions were seen more commonly in the two studies in which the vaccine was administered subcutaneously (31, 32).

Delayed local reactions as seen in the Combination B studies (see Section 2.3.2) occurred in some volunteers in the majority of other trials with antigens formulated in Montanide® ISA720. Over all of the studies approximately 11% of volunteers developed these reactions, which were characterized by pain and swelling at the injection site occurring 10-28 days after vaccination. They resolved without sequelae usually in a few days but in some cases several weeks. There was a trend indicating that the rate and severity of these delayed reactions was increased with higher antigen doses and multiple injections.

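### Previous trial products are barred for only four weeks, so a past recipient of an MSP2 or ISA720 vaccine can be enrolled

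*Protocol*

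**What the plan says.** Two items of section 4.2 concern earlier trial products. Item 9 is "Participation in any clinical trial within the 4 weeks preceding the study". Item 18 is "Receipt on any investigational product four weeks prior to screening".

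The other items that come near the subject are:
- item 1, "History of malaria or malaria exposure within last two years";
- item 7, "History of a severe allergic reaction or anaphylaxis or convulsions following any vaccination";
- item 8, "Receipt of a live vaccine within past 4 weeks or a killed vaccine within past 2 weeks prior to entry into the study".

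Section 4.3 bars other investigational vaccines only during the study. Screening (6.2) takes a full medical history but does not mention past malaria vaccination or ISA720. Blood for the anti-MSP2 ELISA is drawn on day 0 (6.4), but its result does not decide eligibility.

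On earlier use, section 2.3.2 states: "Two Phase I vaccine trials were conducted at the Royal Brisbane Hospital to test the immunogenicity and safety of the Combination B vaccine". Combination B contained a recombinant 3D7 MSP2 and was formulated in ISA720. The same section describes a Combination B challenge trial at that hospital, and section 2.3.3 describes an AMA1/ISA720 trial there. On recruitment, section 4.0 states: "Volunteers will be recruited from the database of healthy volunteers maintained by Q-Pharm". It also allows advertising to University of Queensland students and to the general community.

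**The concern.** A washout suits a drug that is cleared. It does not suit a vaccine, because immune memory can last for years. A person given 3D7 MSP2 in ISA720 years ago passes a four-week rule as easily as someone never vaccinated.

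Two results could be affected.

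- **Immunogenicity.** Section 9.1.3.1 plans contrasts between the two MSP2 serotypes and between doses at each time point, at a nominal 10% error rate without multiplicity correction. Combination B carried only the 3D7 form, so its recipients could be primed to one of the two vaccine antigens. The flanking regions of MSP2 are conserved (section 2.1), so some carry-over to FC27 cannot be excluded, but an unequal advantage is plausible.
- **Local reactions.** Section 2.3.3 reports a trend in which "the rate and severity of these delayed reactions was increased with higher antigen doses and multiple injections". A volunteer with earlier ISA720 injections enters with a different injection history from the others in the cohort.

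With 12 active volunteers per dose, one atypical person is a visible fraction of an arm.

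**Working it through.** The protocol gives no figure on this point, so there is none to reproduce. The check reads the criteria against the earlier trials and then gives a size by illustration.

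**1. Which criterion would stop each group of earlier Brisbane recipients?**

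| Earlier trial | Given | Item 1 | Items 7, 8 | Items 9, 18 |
|---|---|---|---|---|
| Two Combination B Phase 1 trials, sizes not stated | 3D7 MSP2 in ISA720; some had adjuvant alone | No | Not on account of that vaccination, unless it caused a severe allergic reaction, anaphylaxis or convulsions | No, after four weeks |
| Combination B challenge trial, 12 volunteers | 3D7 MSP2 in ISA720, or adjuvant alone, then infected red cells | Depends on reading | As above | No, after four weeks |
| AMA1 trial, 10 + 10 + 9 = 29 volunteers | AMA1 in ISA720, no MSP2 | No | As above | No, after four weeks |

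Item 1 can be read in two ways. If the two-year limit applies only to exposure, any past malaria excludes, and the challenge volunteers are probably barred. If the limit applies to both parts, they are not barred.

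**2. Could earlier recipients still be within the age limit?** Take the publication years in the reference list (1999 for the two Phase 1 trials, 2000 for the challenge trial, 2005 for AMA1) as stand-ins for the vaccination dates. The protocol version is dated 2008 and the upper age limit is 45. The highest age in the publication year that still qualifies is 45 − (2008 − year):
- 1999: 45 − 9 = 36
- 2000: 45 − 8 = 37
- 2005: 45 − 3 = 42

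Vaccination came before publication, so the true ceilings are somewhat lower. Age does not close the gap.

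**3. Illustrative effect on the arm mean.** Suppose one of n = 12 volunteers has a titre f times what it would otherwise be. The arm's geometric mean is multiplied by f^(1/12). The value of f is assumed and has no source in the protocol.
- f = 3: 3^(1/12) = 1.10, a rise of 10%
- f = 10: 10^(1/12) = 1.21, a rise of 21%
- f = 30: 30^(1/12) = 1.33, a rise of 33%

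If only the 3D7 titre is raised, the same factor applies to the arm's 3D7:FC27 ratio.

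**4. Against sampling error.** On the log10 scale the shift is log10(f)/12, which is 0.040, 0.083 and 0.123 for the three values. Assume a between-subject SD of 0.3 to 0.6 log10 (not in the protocol). The standard error of a 12 v 12 dose difference is SD × √(2/12), or 0.12 to 0.24. The shift is then about 0.2 to 1.0 standard errors, against roughly 1.7 needed at the 10% level.

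**5. Adverse-event comparison.** One event in 12 active volunteers is 8.3%. The controls number 3 + 3 = 6 (section 3.2). With a single event among 18 people, it falls in the active arm with probability 12/18 and in the controls with probability 6/18. The two-sided Fisher p-value is 12/18 + 6/18 = 1.0, before any Holm correction.

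**The case against.** The best defence is that this is unlikely to happen and would do limited damage. Nothing links the earlier hospital volunteers to the present database. The protocol's own evidence on priming is mixed: Combination B left anti-MSP2 titres unchanged in adults in Papua New Guinea, although children there did respond. Every active volunteer is primed by the first dose, so a constant fold advantage across three doses is hard to defend. There are partial safeguards: a medical history, the day 0 ELISA, individual graphs for all 30 volunteers, and a repeat analysis with day 0 values as covariate.

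Most of this stands as a limit on size. It does not remove the gap. A low day 0 titre does not rule out memory, the covariate does nothing for local reactions, and no criterion tells staff to ask the question or to exclude on the answer.

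A reader might infer three stronger things that the documents do not support.

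- **That at least 29 + 12 = 41 known people could enter already primed to MSP2.** The 29 had AMA1 only. The 12 include adjuvant-alone recipients and may fall under item 1.
- **That one such person would create or hide a difference.** Steps 4 and 5 of the working do not show this for the dose comparison or for a single adverse event.
- **That the protocol promises a vaccine-naive population.** It says malaria-naive, and that this formulation is untested in humans. First exposure is an inference from the aims, though a reasonable one.

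Items 9 and 18 also run from different reference events, but no consequence of that has been shown.

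**Conclusion.** The gap is real and lies in the wording of 4.2. A recipient of 3D7 MSP2 in ISA720 from either Combination B Phase 1 trial can meet all of 4.1 and 4.2. Whether a challenge-trial volunteer can depends on how item 1 is read.

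The likelihood is unknown and probably low. If one such volunteer enrolled, the arm's geometric mean could rise by 10% to 33%, on the assumption of one person in 12 and a 3- to 30-fold higher titre. That would bias the serotype and dose contrasts, but on the assumed SDs it is within about one standard error of a dose difference. For local reactions the support is a reported trend with higher antigen doses and multiple injections. It is not evidence that past ISA720 with another antigen raises risk in a later trial.

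Eligibility is settled in the protocol, so this cannot be left to the SAP. It is a cheap improvement, and its absence does not invalidate the design.

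**What to change.** Add one exclusion to 4.2: previous receipt, at any time, of a malaria vaccine, an MSP2-containing product or a Montanide ISA720-adjuvanted product, or previous experimental malaria challenge. Naming challenge separately also removes the dependence on how item 1 is read. Add one matching question to the screening list in 6.2. Keep the four-week washout for other investigational products.

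The cost is two lines of text and a few extra screen failures. Section 3.2 already allows for screening up to 150 people to fill 30 places.

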## 4.3 Treatments that could Potentially Interfere with Vaccine-Induced Immunity

Participants’ use of concomitant medications will be checked at each visit. If any of the following criteria become applicable during the study, the participant will be excluded from receiving further doses of the study vaccine and will not be included in the immunogenicity evaluations after the time of exclusion. The participant will, however, be encouraged to remain in the safety evaluation for doses already received.

1. Use of any investigational drug or investigational vaccine other than the study vaccine during the study period.
2. Administration of a licensed vaccine during the period starting from 14 days before to 30 days after each vaccination
3. Administration of chronic (defined as more than 14 days) immunosuppressants or other immune-modifying drugs. (For corticosteroids, this will mean prednisone, or equivalent, greater than or equal to 10 mg/day. Topical and nasal steroids are allowed subject to dose limitations outlined in 4.2 Exclusion Criteria (v).)
4. Administration of immunoglobulins and/or any blood products until the last study visit.

## 4.4 Contraindications to Vaccination

The following criteria should be checked prior to each immunisation and are contraindications to further immunisation. However, the participant will be encouraged to remain in the safety evaluation for doses already received.

1. Hypersensitivity reaction following administration of the study vaccine.
2. Pregnancy, as determined by a positive urine β-hCG.
3. Occurrence of severe chronic disease (such as diabetes or tuberculosis), which in the view of the investigators could jeopardize the safety of study participant or interpretation of the safety or immunogenicity data.

## 4.5 Indications for Deferral of Vaccination

The adverse events (AEs) outlined below constitute grounds for deferral of vaccine administration at that point in time. If any one of these AEs occurs at the time scheduled for vaccination, the participant may be vaccinated at a later date, within the allowable time interval specified in **Section 6.4** of this protocol, or withdrawn at the discretion of the investigator. The participant must be followed until resolution of the event as with any AE. If the participant is withdrawn from the study and has received at least one vaccine dose, he/she will be encouraged to remain in the safety evaluation for the duration of the study.

1. Oral temperature >37.5 °C will warrant deferral of immunisation until fever and causative illness resolve, in the opinion of the investigator.
2. Any other acute condition that in the opinion of the investigator poses a threat to the individual if immunized, or that may complicate interpretation of the safety of the vaccine following immunisation.
3. Such individual(s) will be followed by the investigators until the symptoms resolve or the window for immunisation expires. No further vaccination will be performed if the participant does not recover (oral temperature 37.5 °C and/or lack of symptoms) within the originally scheduled vaccination time interval. If the subject has received at least one dose of vaccine, he/she will be followed for evaluation of safety and immunogenicity. If the individual meets any of the above criteria for deferral on the day of first immunisation, as an alternative to deferral of vaccination, the investigator may instead elect to exclude the volunteer from further participation in the study. Eligible alternate(s) will then be vaccinated instead.

## 4.6 Subject Withdrawal Criteria

A volunteer will not be considered to have completed the trial if any of the circumstances outlined below apply. However, any volunteer who has received at least one dose of vaccine will be encouraged to remain in the safety evaluation for the duration of the study.

1. *Research terminated by sponsor, investigator, or regulatory body* – applies if the study is terminated by a sponsor, investigator, or regulatory body for any reason.
2. *Withdrawal of consent* – applies to a participant who withdraws consent to participate in the study for any reason.
3. *Noncompliant with protocol* – applies to a participant who does not comply with protocol-specific visits or evaluations, on a consistent basis, such that adequate follow-up is not possible and the participant’s safety would be compromised by continuing in the trial.
4. *Significant adverse event* - applies to a participant who is withdrawn from the study by the investigator due to an adverse event, serious or otherwise.
5. *Lost to follow-up* - applies to a participant who consistently does not return for protocol study visits, or who cannot be contacted or located.
6. If *new safety data* becomes available during the trial that impacts participant health.
7. *Pregnancy*. Should a female volunteer become pregnant during the course of the study, she will be withdrawn from the study and followed for the duration of the pregnancy. The outcome of the pregnancy will be documented.
8. If, in the judgment of the investigator, the subject has a condition that would interfere with safety or compliance with follow-up visits.
9. *Other* – is a category used when previous categories do not apply, and requires an explanation.

# 5.0 Vaccine Preparation

## 5.1 Supplies

Vaccine and ISA720 Control for this protocol will be supplied to the study site pharmacist by CSL Limited, where the vaccines were formulated, dispensed and labeled. Clinical Trial Material will be transported at 2o- 8oC from CSL Limited to the study site pharmacy under temperature controlled conditions and will be monitored with a temperature recording device. Upon receipt of Clinical Trial Material shipment, the study site pharmacist will check the shipment contents, complete the requirements for reporting shipment temperature monitoring and sign the enclosed Clinical Trial Material Dispatch Form. By signing this form, assurance will be provided that the vaccine supplies will be handled and stored safely and appropriately; were received undamaged and will only be dispensed to study patients in accordance with the protocol. The study site pharmacy will be responsible for maintaining the appropriate supply of vaccine at the site and will request any necessary additional Clinical Trial Material in writing through the sponsor.

To ensure that the temperature was maintained between 2o- 8oC during transit, the temperature recording device must be immediately returned to CSL Limited, whereby the temperature data will be downloaded and inspected. Written confirmation from CSL Limited will be supplied to the study site regarding the suitability of use for the Clinical Trial Material.

The MSP2-C1/ ISA720 malaria vaccine is supplied as a milky white emulsion in single‑dose vials. Each 5 mL vial contains 0.8 mL, of which 0.5 mL is the intended volume to be injected. 0.5 mL of vaccine contains the equivalent of 0.15 ml of buffer containing antigen emulsified in Montanide® ISA720. The MSP2-C1/ ISA720 vaccine and ISA720 Control conforms to established requirements for sterility, safety and identity.

